## Abstract

**Background:**

The life-time incidence of low back pain is high and diagnoses of spinal stenosis and disc prolapse are increasing. Consequently, there is a steady rise in surgical interventions for these conditions. Current evidence suggests that while the success of surgery is incomplete, it is superior to conservative interventions. A recent survey indicates that there are large differences in the type and intensity of rehabilitation, if any, provided after spinal surgery as well as in the restrictions and advice given to patients in the post-operative period.

This trial will test the hypothesis that functional outcome following two common spinal operations can be improved by a programme of post-operative rehabilitation that combines professional support and advice with graded active exercise and/or an educational booklet based on evidence-based messages and advice.

**Methods/Design:**

The study design is a multi-centre, factorial, randomised controlled trial with patients stratified by surgeon and operative procedure. The trial will compare the effectiveness and cost-effectiveness of a rehabilitation programme and an education booklet for the postoperative management of patients undergoing discectomy or lateral nerve root decompression, each compared with "usual care"using a 2 × 2 factorial design. The trial will create 4 sub-groups; rehabilitation-only, booklet-only, rehabilitation-plus-booklet, and usual care only. The trial aims to recruit 344 patients, which equates to 86 patients in each of the four sub-groups. All patients will be assessed for functional ability (through the Oswestry Disability Index - a disease specific functional questionnaire), pain (using visual analogue scales), and satisfaction pre-operatively and then at 6 weeks, 3, 6 and 9 months and 1 year post-operatively. This will be complemented by a formal analysis of cost-effectiveness.

**Discussion:**

This trial will determine whether the outcome of spinal surgery can be enhanced by either a post-operative rehabilitation programme or an evidence-based advice booklet or a combination of the two and as such will contribute to our knowledge on how to manage spinal surgery patients in the post-operative period.

**Trial Registration:**

Current controlled trials ISRCTN46782945

UK CRN ID: 2670

## Background

Currently we are approaching the end of the Bone & Joint Decade, which at its onset identified low back pain (LBP) as one of its main focuses [1]. Whilst LBP is not a life threatening condition it does affect a large proportion of the population with a point prevalence of between 12-35% and a lifetime prevalence of 49-80%[2]. It is therefore not surprising that it is the second leading cause of sick leave [1], impacting on health care utilisation and contributing to disability and work loss. As such it is one of the most costly health problems facing society. Maniadakis and Gray [2] estimated that there are 3.1 million adults in the UK suffering with LBP each year, costing the UK over £9 billion per annum. Whilst the prevalence of back pain is high, a survey in 1994 by the Office of Population Censuses and Surveys indicated that only 10% of affected individuals attend an NHS outpatient clinic and only 0.5% undergo any surgical intervention[3]. Nevertheless, inpatient treatment, of which surgery is a key component, forms the largest single element of overall expense to the NHS related to back pain[4], possibly as high as 30% of the overall direct cost of back pain[5].

Two of the commonest surgical procedures performed on the spine are discectomies for herniated discs[6,7] and nerve root decompression for spinal stenosis[8]. The rates of both of these interventions are rising, particularly with respect to decompression surgery for spinal stenosis which has been attributed to a growing ageing population [8,9]. The existing literature is sufficiently supportive of the operative management of nerve root stenosis and disc protrusion as to preclude a new trial comparing surgical versus conservative treatment of these conditions [10-16]. However, the success of these surgical procedures and patient satisfaction with the outcome, are variable. In decompression surgery for spinal stenosis, success rates have ranged from 58-69% [7,17,18], with patient satisfaction ranging from 70-81% [9,13,19]. McGregor & Hughes [19] found much lower levels of patient satisfaction which was attributed to unrealistic expectations of surgery. This contrasts with Yee et al[9] who suggested that 81% of patient expectations were met by surgery - however, Yee provided patients with detailed pre-operative information. The approach used to assess satisfaction and type of outcome measures used may also contribute to this variation in findings. It has been suggested that whilst leg pain improves following decompressive surgery, functional improvements are less marked[18,20] and this in turn may impact on quality of life [21], so whilst one outcome is deemed successful others are less so. This suggests that there is scope for improvement, particularly with respect to functional outcome.

Discectomy for disc prolapse has higher success rates, ranging from 65-90%[9,22,23], but residual back and leg pain and recurrent herniation remain the major post-operative problem in lumbar disc surgery [21]. Indeed Soldberg et al [22] reported that 4% of patients got worse after surgery, and Yorimitsu et al [24] indicated that up to 10% had significantly more leg pain and a further 10% had significantly more back pain. In terms of function, Yorimitsu et al [24] noted that only 40% of patients returned to pre-sciatica levels of recreational activity, which concords with the work of Thomas et al [25] which suggested that postoperatively discectomy patients health related quality of life scores remain lower than in the normative population.

The upshot is that more could be done to improve functional outcome and quality of life following both types of surgery. Several approaches have been taken to improve these outcomes including optimising patient selection [1,26,27], refining and exploring new surgical techniques [1,28-31], and lastly improving post-operative care and management [32-34]. In May 2003 a workshop comprising surgeons (both orthopaedic and neurosurgical), physiotherapists, statisticians, economists and epidemiologists was convened to discuss these three different approaches and their relative benefits. The conclusion of this meeting was that there was a paucity of knowledge with respect to post-operative management and that addressing this area may provide significant health impact for this patient population. It was agreed that an important first step was to establish current practice with respect to post-operative management following spinal surgery.

Consequently a national survey of practice in the UK was performed. This revealed wide variation in recommendations to patients by surgeons with respect to activity levels and return to work following surgery [35]. Only 35% of surgeons provided written post-operative instructions; there was limited referral to physiotherapy, with only 45% referring patients to a physiotherapist for an average of 1.8 sessions of treatment; and 18% of surgeons advocated the use of a corset post-operatively, with others restricting sitting or encouraging bed rest. Other studies have also noted marked differences between surgeons in recommendations regarding return to work and lifting [1,36-38]. In summary, although individual surgeons may be certain of their practice, the overall variation in post-operative management suggests uncertainty and the literature reveals limited evidence for current practices.

With the improvements in pain associated with minimal improvements in function [20,24], there is an increasing body of evidence suggesting a need for rehabilitation, with evidence of muscle dysfunction in back pain patients[1,39,40], with further deterioration and damage to the muscles as a result of surgery [41,42]. However, while there appears to be a need for some form of post-operative rehabilitation, our survey suggests that uptake is currently poor in the UK, with many surgeons providing simple advice only [35]. A review [43] identified thirteen controlled trials that compared an active rehabilitation programme with standard post-operative care in patients undergoing spinal surgery. These studies suggested that a vigorous post-operative exercise regime led to a more rapid return to work. However, most of these trials were small (a mean of 72 participants, range 12-212) and the measures of outcome limited. In addition, the statistical analysis was inappropriate in some instances, with emphasis on longitudinal comparisons within trial groups rather than between-group comparisons at follow-up. Since this review a number of further randomised and cohort studies have been performed comparing a range of interventions from self directed stretching and stabilisation exercises [44], behavioural graded activities [1,33,45], neuromuscular training [46], stabilisation classes and mixed therapies [47] and home educated and self management interventions [33,48]. Again many of these studies were underpowered, with many comparing interventions such as exercise with education rather than using the limited post-operative care detailed in the recent UK survey [35] as the comparator. Consequently although differences between treatment arms were noted, it is not clear what their real impact would be with respect to usual care, and often these differences did not persist at long term review which may be related to the low power.

As a consequence there is a range of different practices with respect to post-operative management with limited scientific basis for these interventions. This would suggest that further large rigorously-designed and well-executed randomised trials are required. Using the information obtained from both the survey and literature review such a study would need to consider the use of educational material, some form of rehabilitation, and/or a combination of both and "usual care". To design such a trial however, necessitates the availability of both a standard rehabilitation programme and appropriate education material. Considering educational material initially, a review of the literature, internet and utilising the information from the survey [35] revealed that there was no standard practice and a wide range in the accuracy and extent of information provided. Thus, prior to commencing a trial appropriate educational material had to be developed. Based on the success of "The Back Book" [49,50], it was felt that a booklet may be an appropriate forum to deliver such information, and that making the content evidence-based would help address the general confusion in the publically available information to patients. Therefore, a large literature review into post-operative management was instigated and this was used to synthesise key messages for a post operative educational booklet which was subsequently evolved, evaluated and published [34,51].

The next step was to develop a post-operative intervention that was acceptable to both surgeons and patients. It was not possible to base this on current evidence as this was lacking, with respect to content and timing. At the initial workshop to develop this study, the surgeons were reluctant to discharge their patient directly into a rehabilitation class and the general consensus was that any form of rehabilitation class should start no sooner than 6 weeks post-operatively. Previous post-operative classes had either focused on stretching, resistance training, spine stabilisation exercises or mixed physiotherapy techniques [44,46,47,52]. With little agreement from these studies on what the key exercise content should be and a lack of evidence in the scientific literature the focus of the classes was to get the patient active, and it was decided to base the content on the style of Frost et al[53] Back to Fitness programme, but to extend these twice weekly classes over 6 weeks rather than 4. Based on the success of the Back Café concept described by Christensen et al [54] where patients benefited from meeting and discussing their surgery and progress with other patients, it was decided to include a discussion forum in the rehabilitation classes and for the classes to be of a rolling nature i.e. classes run continuously with patients joining the classes at their own allocated time rather than waiting for a new batch of classes to start. This facilitates patients at different stages of the post-operative journey sharing their experiences with others in the class. To incorporate all of these issues each class will last a maximum of one hour.

With the interventions in place it was possible to design an appropriate trial, the aim of which was to evaluate via a factorial randomised controlled trial, the benefits of a rehabilitation programme and an education booklet for the postoperative management of patients undergoing discectomy or lateral nerve root decompression, each compared with "usual care". The primary aim of this study is therefore, to determine if the long-term functional outcome of spinal surgery and patient satisfaction can be improved via either a systematic programme of post-operative rehabilitation or an educational booklet, and whether a combination of both is even more effective. A secondary objective is to assess whether or not such approaches are cost-effective.

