## Methods/Design

### Trial Design

Function after spinal treatment, exercise and rehabilitation (FASTER) is a multi-centre, factorial, randomised, parallel group controlled trial using validated measures of outcome and with a parallel economic analysis. It involves recruiting and consenting patients with symptoms, signs, and radiological findings of either lateral nerve root compression or disc prolapse scheduled for surgery who will be randomised using a 2 × 2 factorial design to receive:

• Factor 1 - either a six-week programme of post-operative rehabilitation or the relevant surgeon's usual postoperative care, which includes clinical review and perhaps some very limited physiotherapy:

• Factor 2 - either an educational booklet ("Your Back Operation" see below), or the surgeon's usual advice.

This will create 4 groups; rehabilitation-only, booklet-only, rehabilitation-plus-booklet, and usual care only. Allocation to a group will be stratified by surgeon and surgical procedure and allocation will use random permuted blocks within strata. This ensures that each participating surgeon and both surgical procedures will have approximately equal numbers of patients allocated to the 4 groups. Treatment allocation will be concealed to avoid selection bias during recruitment. All patients will be assessed for functional ability, pain, and satisfaction pre-operatively and then at 6 weeks, 3, 6 and 9 months and 1 year post-operatively. This will be complemented by a formal analysis of cost-effectiveness. A summary is provided in figure 1.

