### Trial Sample

This trial has been approved by Hammersmith and Queen Charlotte's & Chelsea Hospitals Research Ethics Committee, with site approval for Ravenscourt Park Hospital, St Mary's Hospital, St Thomas' Hospital, Royal Free Hospital, Heatherwood and Wexham Park Hospital, and Charing Cross Hospital.

Eligible patients include those currently on the waiting list for spinal surgery with either (a) signs, symptoms and radiological evidence of lateral nerve root compression, that is, patients presenting with radicular pain with an associated neurological deficit or with neurogenic claudication (pain in the buttock, thigh or leg that improves with rest), or (b) lumbar disc prolapse, that is, patients with root symptoms and signs and MRI confirmation of lumbar disc herniation. Patients with any of the following will be excluded from participation in the trial; any condition where either the intervention or the rehabilitation may have an adverse effect on the individual; previous spinal surgery; spinal surgery where a fusion procedure is planned due to the unknown hazards of the activity programme for this type of surgery; pregnant women; inadequate ability to complete the trial assessment forms; any patient who is unable to attend the rehabilitation or the reviews or who is unsuitable for rehabilitation classes.

Written informed consent will be obtained from all patients and baseline assessment completed prior to surgery and randomisation into the trial. Patients will be notified of their randomisation following surgery. Those allocated to either the booklet-only group or the rehabilitation-plus-booklet group, will get the "Your back operation" on discharge (see details below).

The trial aims to recruit 344 patients into the trial with 86 patients in each of the 4 sub-groups. This figure was based on being able to detect a 20% relative improvement in the Oswestry Disability Index (version 2.1). We anticipate a mean ODI of 40 in the control group and 32 in the exercise group at 1 year, to have a 90% chance of detecting a between-group difference of 8 points on the ODI and declaring it statistically significant using a two-sided alpha= 0.05, requires a total of 344 patients. This calculation assumes a standard deviation of 20 in each group and allows for loss to follow-up of 23%, as found in earlier descriptive work [20].

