### Proposed Analyses

Analyses will begin with a descriptive comparison of the trial groups before surgery to confirm that randomisation has produced groups that are balanced with respect to known confounders. This will include age, sex, type of surgery, ethnic background, marital status, body mass index, occupation type, work status and smoking status. Pre-operative scores on the primary and secondary outcomes will also be presented by group.

Full functional recovery from back surgery can be protracted, so the primary outcome of interest is the between-group difference in score on the ODI at one-year follow-up, based on intention-to-treat (modified to exclude patients recruited in error). Missing outcome data are expected because of this timeline. Multiple imputation under missing at random [64] will be used for patients with some follow-up but unmeasured one-year outcomes.

Groups will be compared via analysis of covariance, with adjustment for stratifying block using a linear mixed model. If assumptions appear violated, some transformation of the outcome will be taken such that assumptions appear sensible. If this fails, a non-parametric test will be used.

Parallel analyses will be performed for booklet vs. no-booklet and rehabilitation vs. no-rehabilitation, with the sample-size calculation given above applying to each of these. These calculations will be followed by an analysis which tests for an interaction of effect of the two interventions on the primary outcome.

We will check whether the same pattern of outcomes is apparent for patients undergoing lateral nerve root decompression and those undergoing discectomy, and for other subgroups defined by baseline body mass index, baseline HADS score, and single versus multiple anatomic levels of surgery. In addition to the analyses at one year, we will also compare the groups at 6 weeks (beginning of rehabilitation programme in the intervention group) and 3, 6, and 9 months.

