### Interim analysis

As active rehabilitation may potentially produce a worse outcome, there will be an interim analysis once a third of the target number of patients have reached 6 month follow-up, this would allow for 60 patients per group for the main effect of each factor. At this analysis, an independent Data Monitoring Committee (DMC) will apply stopping rules of p < 0.01 for harm, and p < 0.001 for benefit associated with each intervention. We are assuming that there is no interaction between the rehabilitation and booklet however we have requested that the DMC inform us if it becomes apparent that this is not the case. If the DMC recommend stopping recruitment to one of the trial factors only, recruitment and randomisation regarding the other factor will continue but the intervention to which the stopping rule has been applied will be applied (or withheld) for all patients subsequently randomised. For example, if an interim analysis demonstrates a significant beneficial effect of rehabilitation (based on the pre-specified stopping rules), then both the non rehab groups i.e. no rehab no book, book only will be stopped and the remaining trial population will be randomised to either the rehabilitation only or rehabilitation and booklet group.

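### The primary aim includes the benefit of combining the two interventions, but the named analyses answer that only by assuming no interaction, which the trial can barely check

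*Protocol article*

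**What the plan says.** The last paragraph of the Background gives the primary aim. It asks whether rehabilitation or the booklet improves long-term function and satisfaction, and also "whether a combination of both is even more effective". Under Trial Design the factorial allocation is set out: "This will create 4 groups; rehabilitation-only, booklet-only, rehabilitation-plus-booklet, and usual care only".

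Trial Sample sizes the trial on one two-group difference: "We anticipate a mean ODI of 40 in the control group and 32 in the exercise group at 1 year", so as "to have a 90% chance of detecting a between-group difference of 8 points on the ODI". Proposed Analyses then specifies one comparison for each factor, "with the sample-size calculation given above applying to each of these", and adds: "These calculations will be followed by an analysis which tests for an interaction of effect of the two interventions on the primary outcome". No size or power is given for that test. No comparison of the combination with either single intervention is named.

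The Interim analysis section states the assumption behind this approach, "We are assuming that there is no interaction between the rehabilitation and booklet", and asks the monitoring committee to report if it proves untrue.

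**The concern.** An interaction test and a comparison of the combination with a single intervention are different questions. The combination can beat both single interventions with no interaction at all, or even with a negative one. A significant interaction does not by itself show that the combination is better than either intervention alone. The only named analysis that touches the joint effect therefore does not estimate the quantity in the aim.

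The route that remains is indirect. If there is no interaction, each marginal effect is also the gain from adding that intervention to the other. Two beneficial margins then imply that the combination is better than either alone. This is sound reasoning, but it rests on an assumption that a trial sized on the margins checks only weakly. A non-significant interaction test could easily be taken as support for additivity when the data are too few to give it.

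**Working it through.** **Inputs** (Trial Sample unless noted): 344 patients, 86 per cell; difference of 8 ODI points; SD 20; two-sided alpha 0.05; power 90%; loss to follow-up 23%. All power figures use the normal approximation, Φ(effect/SE − 1.96), with the unadjusted SD.

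**1. The plan's own figure.** n per margin = 2 × [20 × (1.960 + 1.282)/8]² = 131.4, rounded up to 132, so 264 evaluable. 264/0.77 = 342.9, so 343, or 344 when made divisible by four. The stated number reproduces.

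**2. Evaluable patients.** 344 × 0.77 = 264.9, which is 132.4 per margin and 66.2 per cell.

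**3. Standard errors.**
- Marginal effect: 20 × √(2/132.4) = 2.46
- One cell against another: 20 × √(2/66.2) = 3.48
- Interaction (a difference of two cell differences): 20 × √(4/66.2) = 4.92

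**4. Power.**

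| Contrast | 4 points | 8 points | 12 points | 16 points |
|---|---|---|---|---|
| Interaction | 13% | 37% | 68% | 90% |
| Combination against one single intervention | 21% | 63% | – | – |

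The marginal effect has 90.2% power for 8 points. For the interaction at 8 points: 8/4.92 − 1.96 = −0.33, and Φ(−0.33) = 0.37. For the cell contrast: 8/3.48 − 1.96 = 0.34, and Φ(0.34) = 0.63. If the effects are fully additive at 8 + 8 points, the chance that the combination is significantly better than both single interventions is about 48% (by simulation).

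**5. What sub-additivity does to the margins.** Suppose each intervention alone gives 8 points and the combination falls short of 16 by I points. Each marginal effect is the mean of 8 and 8 − I, that is 8 − I/2.

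| Shortfall I | Marginal effect | Marginal power |
|---|---|---|
| 0 | 8 | 90% |
| 2 | 7 | 81% |
| 4 | 6 | 68% |
| 8 | 4 | 37% |

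With 4 points of synergy the marginal effect is 10 and the power 98%. The documents give no figure for the size or direction of any interaction, so these are scenarios.

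**6. The interim safeguard.** The Interim analysis section gives 60 patients per group for each main effect, so about 30 per cell. If the SD is also 20 at 6 months (an assumption), the interaction SE is 20 × √(4/30) = 7.30. Power for 8 points is then Φ(8/7.30 − 1.96) = Φ(−0.86), about 19%.

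**The case against.** The strongest reply is that this is how a factorial trial works. The no-interaction assumption is stated openly, and under it the two margins do answer the combination question. Low power for the interaction is common to every trial sized on its margins. That stands, and it limits the point: the aim is answered conditionally. A reader might infer that part of the aim goes unanswered, but the documents do not support that.

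A reader might also infer that the stated 90% holds only if effects are additive. This is wrong. Trial Sample ties the 90% to a difference of 8 points, and Proposed Analyses applies it to the marginal comparisons. It is correct whenever the marginal effect is 8 points, with or without an interaction, and it is exceeded under synergy. It falls only if 8 points is the effect of each intervention alone and the effects are sub-additive.

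Two further complaints carry little weight.
- Running the factor comparisons in parallel does not exclude a joint model, and the interaction test needs one. Even if an 8-point second factor were left out, the variance would rise by 4²/20² = 4% and power would go from 90% to about 89%.
- Half of each marginal control group receives the other intervention, but that is inherent in the design and does not contradict the comparison with usual care.

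The planned analysis of covariance may also help. If it adjusts for baseline ODI with a correlation of 0.5 (an assumption), the SD becomes 20 × √0.75 = 17.3. The 8-point powers then rise to about 47% for the interaction and 76% for the cell contrast. That is better, but still short of 90%.

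Finally, cell means and contrasts may sit in an analysis plan that is not shown, so their absence alone would be no finding. The point rests on what this document fixes itself: an aim that includes the combination, and a list of primary-outcome comparisons that reaches it only through an assumption.

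**Conclusion.** The aim and the named analyses do not match. Whether the combination beats either intervention alone is addressed only under an assumption of no interaction, and the trial has about 37% power to detect a departure as large as its planned main effect. That 37% depends on taking 8 points as the interaction; the range is 13% to 90% for 4 to 16 points. A direct comparison of the combination with one single intervention has about 63% power for 8 points. These figures assume 23% loss, SD 20 and no gain from covariate adjustment.

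The sample size is not in error. Nor does the document say that a non-significant interaction will be read as proof of additivity; the concern is that nothing in it guards against that reading. Sub-additivity is possible, since the classes include some advice. However, the booklet is given at discharge and the classes start 6 to 8 weeks after surgery, so the overlap is uncertain. The change is worth making because it is cheap and lets the trial answer its own question directly.

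**What to change.** - From the model with both factors and their interaction, report the four cell means. Pre-specify the combination against rehabilitation only, against booklet only and against usual care, each with a confidence interval.
- In Trial Sample, state that the 90% applies to a marginal difference of 8 points. Add that if each intervention alone gives 8 points but effects are sub-additive, it falls to 81%, 68% or 37% for shortfalls of 2, 4 or 8 points.
- State that a combination-against-single contrast of 8 points has about 63% power, and give the interaction power with the effect size it refers to.
- State that a non-significant interaction is not evidence of additivity.
- If an analysis plan already contains these contrasts, align Proposed Analyses with it.

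The cost is some wording and a few contrasts from a model that is already planned. No extra patients are needed. The downside is a less favourable stated power for the combination question.
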